**Table 4: Blinding and Unblinding Plan**

| Role                                                                                                                          | Randomization list generated | Treatment allocation & dosing | Safety event (single participant unblinded) |
|-------------------------------------------------------------------------------------------------------------------------------|------------------------------|-------------------------------|---------------------------------------------|
| Participants                                                                                                                  | B                            | B                             | UI                                          |
| Rater Only staff                                                                                                              | B                            | B                             | UI                                          |
| Unblinded site staff e.g. pharmacy staff and data entry                                                                       | B                            | UI                            | UI                                          |
| Vaccine Clinical Supply and Randomization                                                                                     | UI                           | UI                            | UI                                          |
| Unblinded sponsor staff or designee e.g. for study treatment resupply, unblinded monitor(s), sample analyst(s)                | B                            | UI                            | UI                                          |
| Unblinded Pharmacovigilance sponsor staff or designee                                                                         | B                            | UI                            | UI                                          |
| Statistician/statistical programmer/ data analysts (e.g. immunogenicity)                                                      | B                            | UI                            | UI                                          |
| All other sponsor staff not identified above (i.e. trial team, project team, management & decision boards, support functions) | B                            | UI                            | UI                                          |

Key:

UI: Allowed to be unblinded on individual participant level

B: Remains blinded

NA: Not applicable to this study

## 6.5 Dose escalation and dose modification

Investigational or other study treatment dose adjustments and/or interruptions are not permitted.

## 6.6 Additional treatment guidance

### 6.6.1 Treatment compliance

VX-103 will be administered at the study site. The site must maintain an accurate record of the receipt and of dispensing of study treatment in a drug accountability log. Note: study treatment includes investigational product and placebo.

Immunogenicity parameters will be determined in all participants treated with VX-103, as detailed in Section 8.5.1 Immunogenicity.

### 6.6.2 Recommended treatment of adverse events

At present there is insufficient information to provide specific recommendations regarding treatment of AEs.

In the case of unanticipated AEs, the investigator should consider the criteria for study interruptions (see Section [9.1 Discontinuation and completion](#)).

Medication, including the use of acetaminophen that is used to treat AEs must be recorded on the appropriate eCRF.

### **6.6.3 Emergency breaking of assigned treatment codes**

Emergency breaking of the assigned treatment code must only be undertaken when it is essential to treat the participant safely and efficaciously.

Most often, study treatment discontinuation and knowledge of the possible treatment assignments are sufficient to treat a study participant who presents with an emergency condition. Since only the rater and subject are blinded, the site will maintain a copy of the randomization and treatment list in a secure location. Should a blind need to be broken, the site staff will follow their local procedures and will notify the Sponsor immediately. The investigator must also immediately inform the sponsor's local monitor that the code has been broken.

It is the investigator's responsibility to ensure that there is a dependable procedure in place to allow access to break the blind at any time in case of emergency. The investigator will provide:

- protocol number
- participant number

In addition, oral and written information to the participant must be provided on how to contact the investigator's backup in cases of emergency, or when he/she is unavailable, to ensure that un-blinding can be performed at any time.

### **6.7 Preparation and dispensation**

Each study site will be supplied with investigational product in packaging as described under investigational and control drugs section (as described in Section [6.1.1 Investigational and control product](#)).

Clinical supplies are to be dispensed only in accordance with the protocol. For preparation of study treatment, the unblinded pharmacist or authorized designee will access the treatment allocation from the provided randomization list. Study vaccine delivered by MIMIX MAP (VX-103 or placebo) will be prepared by an unblinded local pharmacist or designee at the study site.

Please refer to the pharmacy manual for detailed instructions on drug preparation and administration. Appropriate documentation of the participant-specific dispensing process must be maintained.

## **7 INFORMED CONSENT PROCEDURES**

Eligible participants may only be included in the study after providing (witnessed, where required by law or regulation), institutional review board/ independent ethics committee (IRB/IEC)-approved informed consent.

If applicable, in cases where the participant's representative(s) gives consent (if allowed according to local requirements), the participant must be informed about the study to the extent possible given his/her understanding. If the participant is capable of doing so, he/she must indicate agreement by personally signing and dating the written informed consent document.

Informed consent must be obtained before conducting any study-specific procedures (e.g. all of the procedures described in the protocol). The process of obtaining informed consent must be documented in the participant source documents.

Vaxess or designee will provide to investigators in a separate document a proposed informed consent form that complies with the ICH GCP guidelines and regulatory requirements and is considered appropriate for this study. Any changes to the proposed consent form suggested by the investigator must be agreed by Vaxess or designate before submission to the IRB/IEC.

Information about common side effects already known about the investigational product can be found in the IB. This information will be included in the participant informed consent and should be discussed with the participant during the study as needed. Any new information regarding the safety profile of the investigational product that is identified between IB updates will be communicated as appropriate, for example, via an investigator notification or an aggregate safety finding. New information might require an update to the informed consent and then must be discussed with the participant.

The following informed consents are included in this study:

- Main study consent, which also includes:
  - A subsection that requires a separate signature for the 'Optional Consent for Additional Research' to allow future research on data/samples collected during this study
- As applicable, Pregnancy Outcomes Reporting Consent for female participants or the female partners of any male participants who took study treatment

Male participants must be informed that if a female partner becomes pregnant while he is enrolled in the study, contact with the female partner will be attempted to request her consent to collect pregnancy outcome information.

A copy of the approved version of all consent forms must be provided to Vaxess or designate after IRB/IEC approval.

## **8 VISIT SCHEDULE AND ASSESSMENTS**

The Assessment Schedule ([Table 5](#)) lists all assessments and when they are performed. All data obtained from these assessments must be supported in the participant's source documentation.

Participants should be seen for all visits/assessments as outlined in the assessment schedule ([Table 5](#)) or as close to the designated day/time as possible. Missed or rescheduled visits should not lead to automatic discontinuation. Participants who prematurely discontinue the study for any reason should be scheduled for a visit as soon as possible, at which time all of the assessments listed for the final visit will be performed. At this final visit the adverse event and concomitant medications will be recorded on the eCRF.

The preferred sequence of data collection during study visits is vital signs and followed by blood sampling.

Every effort will be made to take the immunogenicity sample at the protocol specified time. Other assessments e.g. vital signs, etc. will be taken prior to the immunogenicity sample.

[illegible]

|                                                                                                        |   |            |   |   |   |   |   |   |   |     |     |     |   |   |     |  |   |
|--------------------------------------------------------------------------------------------------------|---|------------|---|---|---|---|---|---|---|-----|-----|-----|---|---|-----|--|---|
| ILI Surveillance                                                                                       | X | X          |   |   |   |   |   |   |   |     |     |     |   |   |     |  |   |
| Photographs of Treatment Site                                                              |   | X          | X | X | X | X | X |   | X | X   | X   | X   |   |   | X   |  |   |
| Solicited Local AEs Appendix 1                                                                         |   | X          | X | X | X | X | X | X | X | X*  | X*  | X*  |   |   | X*  |  |   |
| Solicitied Local AEs Appendix 2                                                                        |   | X          |   |   | X | X | X | X | X | X** | X** | X** |   |   | X** |  |   |
| Solicited Systemic AEs Appendix 3                                                                      |   | X          |   |   | X | X | X | X | X |     |     |     |   |   |     |  |   |
| Adverse Event Collection (Unsolicited) m                                                    | X | Days 1-29  |   |   |   |   |   |   |   |     |     |     |   |   |     |  |   |
| SAEs, MAEs and NOCMCs                                                                                  |   | Days 1-180 |   |   |   |   |   |   |   |     |     |     |   |   |     |  |   |
| Serum for Serological Immunogenicity Assays: HAI Titers                                                |   | X          |   |   |   |   |   |   |   |     | X   | X   | X | X | X   |  | X |
| Serum for Exploratory Endpoints: HAI Drifted Strain; Anti HA IgG, Anti- Fibroin IgG, IgE and MN Titers |   | X          |   |   |   |   |   |   |   |     | X   |     |   |   | X   |  | X |
| Safety Telephone Contact n                                                                  |   |            |   |   |   |   |   | X |   |     |     |     |   |   |     |  |   |

\*Erythema assessments only from [Appendix 1: Local Tolerability Scoring](#)  
\*\*Coloration assessment only from [Appendix 2: Other Local Tolerability Scoring](#)

- a. The signed informed consent of the subject must be obtained before study participation.
- b. Record demographic data such as year of birth, sex, race (ethnicity and geographic ancestry) in the subject’s eCRF
- c. Obtain the subject’s medical history by interview and/or review of the subject’s medical records and record any pre-existing conditions or signs and/or symptoms present in a subject prior to the first study vaccination in the eCRF.
- d. Perform a physical examination of the subject, including assessment of oral body temperature and resting vital signs: systolic/diastolic blood pressure, heart rate and respiratory rate after at least 5 minutes of rest, pulmonary auscultation. Collected information needs to be recorded in the eCRF. Any findings from the(se) physical examination(s) need to be recorded in the subject’s medical record, in the medical history screen of the eCRF or reported as an AE or SAE, as applicable, if they meet the protocol definition of AE or SAE. Treatment of any abnormality observed during physical examination has to be performed according to local medical practice outside this study or by referral to an appropriate specialist. After the screening visit, an abbreviated physical exam should be performed at each visit until the final study visit.

- 
- e. All participants will be questioned about concomitant medications at each visit. Medications taken within 30 days prior to day 1 will be documented in the eCRF. Any changes to a subject's medications will also be documented in the eCRF.
- f. The time of placement and removal of the MIMX-MAP will be recorded in the eCRF. The unblinded site staff shall refer to the pharmacy manual for specific instructions. VX-103-01 MAP should be placed on the skin for a minimum of 5 minutes and a maximum of 10 minutes
- g. Vital signs measurements include temperature, respiration rate, heart rate, and blood pressure after a 5-minute seated rest.
- h. Hematology: will be drawn and analyzed locally. The data will be captured in the eCRF and the lab reports stored with the subject's source documents at the site.
- i. Chemistry: will be drawn and analyzed locally. The data will be captured in the eCRF and the lab reports stored with the subject's source documents at the site.
- j. Female participants of childbearing potential are to have a urine pregnancy test prior to any study vaccine administration. The test result is to be recorded in the eCRF. The investigational product/products may only be administered if the pregnancy test is negative. A serum pregnancy test instead of a urine pregnancy test should only be considered if required by country, local or ethics committee regulations. If a serum pregnancy test instead of a urine pregnancy test is required by country, local or ethics committee regulations, a blood sample will be collected from women of childbearing potential at the vaccination visits and will be used for the test as per local guidance. Note: Pregnancy test must be performed even if the subject is menstruating at the time of the study visit.
- k. At minimum, a basic urine alcohol & drug screen will be used to analyze for amphetamines, Opiates, Phencyclidine (PCP), Cocaine, Marijuana, and alcohol.
- l. All photographs should be taken with the study specific iPhone or the study specific DermLite DL4 Dermatoscope attached to the iPhone. Subject ID, Subject initials, and timepoint should be included in each iPhone photograph with a label. On Study Day 1, iPhone photographs should be taken of the treatment site both pre dosing (within 30 minutes prior to dosing) and 1 + 2 minutes, 30 ± 5 and 60 ± 5 minutes post removal of the MAP. iPhone photographs will also be taken a single time on Days 2, 4, 8, 15, 29, 57 and 180. For each iPhone photograph hold the phone 8-10 cm above the Application site, take one, in focus, 1x magnification photo. Capture the Application site and label.
- Dermatoscope images will be taken with the Dermatoscope attached to the iPhone, the lens spacer rotated to '0' and the faceplate removed. The image will be taken with the lens spacer gently touching the application site periphery. The rim of the Dermatoscope lens spacer should be wiped with alcohol before and after use. Photographs with the Dermatoscope attached to the iPhone should be taken of the treatment site pre dosing (within 30 minutes prior to dosing) and a single time on Days 29 and 180. Photographs with the Dermatoscope should be 'captioned' using the iPhone 'add a caption' function. The Caption should include the Subject ID, initials and timepoint. All photos should be taken under consistent lighting conditions. All photographs will be uploaded to a secure file system, BOX. Please see VX-103-01 Imaging Instructions for additional instructions.
- m. Standard adverse event collection will take place from the time the informed consent is signed through Day 29. This will capture all adverse events that are not included from the solicited adverse event collection appendices.
- n. These calls are to query for any adverse events, complete Appendix 1, 2 and the systemic section of Appendix 3 and determine if an on-site visit is needed.

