| 
 
To assess the immunogenicity of VX-103 delivered in a single MIMIX MAP dose regimen in healthy adults in <math>\geq 18</math>-39 years of age.
 
To assess VX-103 MIMIX MAP delivery as a dose sparing skin immunization strategy by comparing the safety, reactogenicity, tolerability and immunogenicity of a fractional H1 vaccine dose level (7.5 <math>\mu\text{g}</math>) delivered by MIMIX MAP to a standard H1 vaccine dose level (15 <math>\mu\text{g}</math>) delivered by MIMIX MAP.
 
 |  | 
 
Influenza A H1 geometric mean HAI titer; mean fold rise and seroconversion rates for each treatment group and timepoint on Days 1, 29, 57, 85, 119, 180.
 
MIMIX MAP dose level comparisons in vital signs, laboratory parameters of hematology, clinical chemistry, urinalysis, adverse events, and local and systemic solicited and unsolicited reactogenicity event(s)
 
Influenza A H1 geometric mean HAI titer; mean fold rise and seroconversion rates for each route and timepoint for the fractional dose versus full dose delivered by MIMIX
 
 |  |
| Exploratory objective(s)                                                                                                                                                                                                                                                                                                                                                                                                                                                                                                                                  |  | Endpoint(s) for exploratory objective(s)                                                                                                                                                                                                                                                                                                                                                                                                                                                                                                                                                                              |  |

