| 
 
To assess seroprotection rates, anti-H1 HA IgG, virus microneutralizing (MN) titers, anti-fibroin IgG and total IgE titers to the influenza vaccine
 
                                                                                                                                                                                                                                                                                                                                                     |  | 
 
Influenza A H1 seroprotection rate for each treatment group on Days 1, 29, 180 by HAI and anti-influenza A H1 HA GMT, virus MN titers, anti-fibroin IgG, and total IgE for each treatment group on Days 1, 29, 180
 
                                                                                                                                                                                                                                                                                                                                                  |  |
| 
 
To evaluate the durability of the immune response for each vaccine dose level
 
                                                                                                                                                                                                                                                                                                                                                                                                                           |  | 
 
Influenza A H1 seroconversion rate, GMT, fold increase in GMT and SPR by HAI on Days 29 and 180 for treatment group
 
                                                                                                                                                                                                                                                                                                                                                                                                                                                 |  |

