### **12.1 Analysis sets**

For all analysis sets, participants will be analyzed according to the study treatment(s) received.

The safety analysis set will include all participants who received any study treatment.

The immunogenicity analysis set will include all participants with at least one available valid (i.e. not flagged for exclusion) immunogenicity concentration measurement, who received any study drug and with no protocol deviations that impact immunogenicity data.

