### 12.5.3 Immunogenicity

Although clinical efficacy trials of new influenza vaccines may be performed in late-stage development or post-licensure, FDA licensure can be achieved based upon antigen specific HAI titers. The primary immunogenicity analyses will assess HAI GMTs, GMT mean fold rise, seroconversion rates (defined as a fourfold rise in HAI titers) and seroprotection status (defined as an HAI titer of  $\geq 1:40$ ), by HAI.

HAI antibodies in serum will be determined at specific time points for all participants, including the placebo group and all immunogenicity results will be listed by treatment group, ethnicity, participant and visit/time. Summary statistics may be provided as appropriate in case of high incidence of positive participants/samples.

Sera analyzed for determination of HAI titers will be evaluated as follows:

- Calculation of the geometric mean of pre- and post-vaccination HAI titers for each treatment group.
- Change from pre- to post-vaccination in geometric mean HAI titers for each treatment group.
- Seroconversion rate defined as percentage of participants with either a pre-vaccination HAI titer  $< 1:10$  and post vaccination HAI titer of  $\geq 1:40$  or a pre-vaccination HAI titer of  $\geq 1:10$  and a minimum four-fold rise in post vaccination HAI antibody titer at each timepoint.
- Seroprotection rate defined as the percentage of participants with a HAI titer  $\geq 1:40$  at each timepoint for the vaccine H1 strain

Incidence of positive participants and correlation with selected AEs and clinical outcomes may be explored as appropriate in case of high incidence.

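### Influenza-like illness is checked only up to dosing as Table 5 is printed, while HAI is read to Day 180, so a natural H1 infection may be counted as seroconversion or durability

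*Protocol*

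**What the plan says.** Section 8 presents Table 5 as the full list of assessments and their timing. Its row reads "ILI Surveillance | X | X", with every later cell blank. The row has no footnote, and influenza-like illness (ILI) appears neither in the visit-by-visit text of Section 3 nor in the abbreviation list.

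The HAI endpoints run much longer. Table 1 sets geometric mean titer, "mean fold rise and seroconversion rates for each treatment group and timepoint on Days 1, 29, 57, 85, 119, 180". An exploratory objective is "To evaluate the durability of the immune response for each vaccine dose level", read from HAI on Days 29 and 180. Section 12.5.3 defines seroconversion for those with a measurable baseline titer as "a minimum four-fold rise in post vaccination HAI antibody titer at each timepoint", and says nothing about influenza caught during follow-up.

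On illness capture, Table 5 footnote m states: "Standard adverse event collection will take place from the time the informed consent is signed through Day 29". The synopsis (Study Design) and the Table 5 row agree with Day 29. After that, Table 5 lists only SAEs, MAEs and NOCMCs to Day 180, and the last two terms are not defined. The synopsis (Safety Assessments) and Section 10.1.1, however, have adverse events asked about at every visit, and footnote e does the same for concomitant medication.

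The immunogenicity set in Section 12.1 takes participants with a valid, unflagged measurement and "with no protocol deviations that impact immunogenicity data". It does not say what causes a measurement to be flagged.

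**The concern.** HAI does not show whether an antibody rise came from the patch or from an H1 infection. Participants have had no influenza vaccine for 24 months and may not receive one during the study (Section 5.2), so they remain open to infection for six months. The protocol treats influenza history as relevant at entry, excluding a diagnosis in the previous 24 months, but as printed asks nothing comparable after dosing.

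An unrecognised infection in a dose arm would look like a late response or a well-kept titer. In the placebo arm it would look like seroconversion without antigen. Late titers matter for this product: Section 1.2 bases the rationale on prolonged antigen release and on preclinical HAI trends beyond one month. Illness data that were never collected cannot be recovered by any later analysis plan.

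**Working it through.** **Reading the row.** The column header of Table 5 is not legible in the available text, so the columns have to be placed from other rows.

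- Photographs are marked in columns 2 to 7, 9 to 12 and 15. This matches pre-dose, 1, 30 and 60 minutes, Days 2 and 4, then Days 8, 15, 29 and 57, then Day 180. The telephone contact sits in column 8.
- HAI is marked in columns 2, 11 to 15 and 17. This matches Day 1 pre-dose, Days 29, 57, 85, 119 and 180, and one further column.
- Column 2 is therefore Day 1 before dosing, and the ILI row is marked in columns 1 and 2 only.

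**Uncovered time.** From Day 29 to Day 180 is 180 − 29 = 151 days, out of 180 − 1 = 179 days of follow-up (84%). Under footnote m, non-serious illness in that span has no routine collection unless it falls under MAEs or NOCMCs.

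**Size.** The plan states no attack rate, so there is no figure to reproduce. Inputs are 15 per arm and 45 in total (Table 2, Section 12.8). The risk p of H1 infection over follow-up is an assumption, taken as 1% to 10%. With b(x) the binomial probability of x infections in 15:

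- at least one in an arm: 1 − (1 − p)^15
- at least one in the trial: 1 − (1 − p)^45
- unequal counts in the two dose arms: 1 − Σ b(x)²
- at least one among 30 active, none among 15 placebo: [1 − (1 − p)^30] × (1 − p)^15

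| p | arm of 15 | all 45 | dose arms unequal | active only |
|---|---|---|---|---|
| 1% | 14% | 36% | 24% | 22% |
| 2% | 26% | 60% | 40% | 34% |
| 5% | 54% | 90% | 63% | 36% |
| 10% | 79% | 99% | 75% | 20% |

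These are chances that infection occurs, not that it goes unrecognised, which is less likely.

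**Effect of one case.** If the infected participant would not otherwise have seroconverted, the arm's rate moves by 1/15 = 6.7 percentage points (two cases: 13.3). If infection adds an f-fold rise in one participant, the arm's geometric mean fold rise is multiplied by f^(1/15): 1.10 for 4-fold, 1.20 for 16-fold, 1.26 for 32-fold.

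**Effect on active versus placebo.** Suppose risk p is equal in all arms, infection is independent of vaccine response, and every infection gives seroconversion. A rate s then becomes s + (1 − s)p, so a difference between arms is multiplied by (1 − p): 0.98, 0.95 or 0.90 at 2%, 5% or 10%. In expectation the contrast narrows slightly and is not inflated.

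**The case against.** **The table may be damaged.** The header is unreadable, and merged cells print in column 2, as the rows showing Days 1-29 and Days 1-180 do. A merged ILI cell reaching Day 180 cannot be excluded. Against this, both of those rows carry a day range and the ILI row carries a plain X. The caveat stands, and the first step is to look at the original table.

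**Other routes would find some cases.** SAEs and MAEs run to Day 180, medication is asked about at each visit, participants are told to call with health concerns (Section 3), and two places call for adverse-event questioning at every visit. A reader might infer that no illness is recorded after Day 29; the documents do not support that. They contradict each other on it, so capture is uncertain.

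**Exclusion is possible.** A reader might infer that post-infection titers must stay in every analysis. Section 12.1 allows measurements to be flagged, and the SAP, which was not available, may give the triggers. But flagging for infection needs illness data to act on.

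**Placebo is a concurrent control.** All arms are bled for HAI on the same schedule (Sections 8.3 and 8.5.1), so background H1 exposure is visible. A reader might infer a bias in favour of the vaccine. The calculation does not show one, and if the vaccine protects, extra placebo infections would understate it. What remains is that placebo cannot correct a within-arm rate or a chance imbalance between the two doses, and with 15 participants it may show no infection when the dose arms have some.

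**Importance.** This is a 45-person first-in-human study with a safety primary objective, and durability is exploratory. That limits the weight of the point.

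**Conclusion.** The point holds in a limited form. As printed, ILI is not checked after dosing, and the protocol disagrees with itself on whether ordinary illness is collected after Day 29. A natural H1 infection may therefore be counted as seroconversion or durability. It would be too strong to say that it will be: an infection has to occur and also go unrecognised.

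The exposed results are the late within-arm rates and the realised 7.5 versus 15 µg comparison. One case is worth up to 6.7 percentage points of an arm's seroconversion rate, and the chance of at least one infection per arm is 26%, 54% or 79% at assumed attack rates of 2%, 5% or 10%. Those chances rest wholly on the assumed rates, since the protocol gives neither an attack rate nor an enrolment season. The primary safety objective is not threatened. The change is still worth making because it is cheap and the information cannot be recovered afterwards.

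**What to change.** 1. Confirm the ILI row against the original Table 5. If it was meant to span the follow-up visits, print it so.
2. Otherwise extend it to the existing post-dose visits through Day 180, recording onset date and any influenza test result.
3. Reconcile the Day 29 limit on unsolicited adverse events (synopsis Study Design, Table 5, footnote m) with the every-visit questioning in the synopsis Safety Assessments and Section 10.1.1, and define MAE and NOCMC.
4. Keep the main HAI analysis as planned. Report ILI and confirmed influenza counts by arm. Add a sensitivity analysis of the HAI and microneutralization endpoints that excludes titers after a confirmed influenza illness, with suspected illness shown separately.
5. Do not drop titers because of a four-fold HAI rise between visits. That selects on the outcome and could remove the late response that a prolonged-release product is meant to show. At most, list such rises by arm.

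The cost is one extra eCRF question per visit, one further table and slightly fewer late titers in that table, with no new visit, blood draw or assay. Asymptomatic infections will still be missed.
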